**METHOD**

**Data source, study design, and study population**

This cohort study will be based on the nationwide histopathology cohort, Epidemiology Strengthened by histoPathology Reports in Sweden (ESPRESSO)^1^, and several healthcare registers in Sweden. ESPRESSO^1^ contains data on GI-related biopsies from all 28 pathology departments in Sweden from 1965 to 2017. The Total Population Register^2^ contains details on birth, death, and migration, which was initiated in 1968. The Prescribed Drug Register^3^ collects information on medications dispensed at all pharmacies in Sweden since July 2005, including for example dispensing date, drug name, and a defined daily dose (DDD). The National Patient Register^4^ covers data on inpatient (since 1964) and outpatient (since 2001) specialist care with disease diagnoses and surgical procedures. The Cancer Register^5^ contains data from >96% of incident cancer cases since 1958. The Cause of Death Register^6^ contains information on >99% of death since 1952. The Swedish Longitudinal Integrated Database for Health Insurance and Labour Market Studies^7^ contains information on demographic and socioeconomic characteristics (e.g., education and county of residence).

The IBD patients will be identified as those with ≥ 1 biopsy indicating IBD in the ESPRESSO and ≥ 1 International Classification of Disease (ICD) code for IBD in the NPR (see **Table 1** for the definition of IBD subtypes)^8^. Such diagnostic approach yields a positive predictive value of 95%^9^.

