**Identification of statin users**

Statin use will be identified from the Prescribed Drug Register by the Anatomical Therapeutic Chemical (ATC) code C10AA, including lipophilic statins (simvastatin and atorvastatin) and hydrophilic statins (pravastatin and rosuvastatin) (see **Table 2** for ATC codes). Statin users will be identified as those aged ≥ 18 years and with a statin prescription for ≥30 cumulative DDD (cDDD) from July, 2006 or later. The date that an individual first attained a cDDD ≥ 30 for a statin will be defined as the index date for statin exposure. Individuals who had any statin prescription before July 2006, before IBD diagnosis or before the first attainment of cDDD ≥ 30 will be excluded from the analysis to ensure a new-user design. We will use the intention-to-treat analysis as the main analysis.

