**Two-step matching process**

A two-step matching process will be applied to establish the cohort. In the direct matching step, statin users and non-statin users will be matched on age at IBD diagnosis (<18, 18-<40, 40-<60, and ≥60), sex, IBD subtype (CD or UC), and calendar year at IBD diagnosis (1969-1989, 1990-1999, 2000-2009, 2010-2018). IBD-unclassified will not be considered in this project due to diagnostic uncertainty. To ensure similar opportunities for care and treatment^10^, non-statin users should have a random drug prescription (except IBD medications, see **Table 2** for ATC codes) within three months before or after the start date of statin treatment in the matched statin users. All identified non-statin users will be assigned the same index date as the index statin user. We will exclude individuals who had a record of migration, received a colectomy, or had a diagnosis of any of the following diseases before the index date: cancers, human immunodeficiency virus/ acquired immunodeficiency syndrome, primary immunodeficiency disease, end-stage renal disease, severe liver failure, and any organ transplantation (see **Table 2** for procedure and ICD codes).

In the propensity score matching step, statin users and non-statin users will be matched in a 1:1 ratio by using a greedy nearest-neighbor matching algorithm without replacement, with a caliper of 0.2 standard deviation of the logit of the propensity score^11^. A logistic regression model will be used to calculate the propensity score after adjusting for the below demographic and socioeconomic characteristics, comorbidities, and co-medications identified up to and including the index date.

- Age at IBD diagnosis, years (continuous);
- Duration of IBD, years (continuous);
- Number of healthcare visits (continuous);
- Country of birth (Nordic countries or others);
- Education (0-9, 10-12, ≥13 years, or missing);
- Comorbidities (yes/no, see Table 2 for detail): gastrointestinal diseases, intestinal infections, cardiovascular diseases, obesity/dyslipidemia, type 1 and type 2 diabetes, autoimmune diseases, obstructive sleep apnea, chronic obstructive pulmonary disease, and myositis;
- Medications (yes/no, see Table 2 for detail): antibiotics, proton pump inhibitor, antiviral medications, IBD medications, non-aspirin anti-platelet medications, aspirin, non-statin lipid lowering medications, anti-diabetic medications, anticoagulation medications, and anti-arrhythmias medications.

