| Rosuvastatin | C10AA07 |
| **Outcomes** | **ICD code** ^a^ |
| Incident colorectal cancer (CRC) ^b^ | ICD-7: 153-154, but not 1541 (anal cancer) or 1534 (appendiceal cancer) |
| CRC-related mortality | ICD-10: C18-20, but not C181 (appendiceal cancer) |
| All-cause mortality | ICD-10: A00-U99 |
| **Proctocolectomy and colectomy** | **Procedure code** |
| Proctocolectomy ^c^ |  |
|  | Sixth version (1969-1996): 4652, 4653, 4654 |
|  | Seventh version (1997-): JFH20-JFH40 |
| Colectomy with an intact rectum ^d^ |  |
|  | Sixth version (1969-1996): 4650, 4651 |
|  | Seventh version (1997-): JFH00, JFH01, JFH10, JFH11, JFH96 |
| Rectum amputation after a colectomy with an intact rectum ^e^ |  |
|  | Sixth version (1969-1996): 4820, 4821, 4822, 4828 |
|  | Seventh version (1997-): JGB00-JGB97 |
| **Exclusion criteria** | **ICD-10 code/procedure code** |
| Cancer | C00-C97, except non-melanoma skin cancer (C44) |
| HIV/AIDS | B20-B24, F024, O987, R75, Z114, Z219, Z711 |
| Primary immunodeficiency disease | D71, D80–D84 |
| Severe liver failure | B150, B160, B162, B190, K704, K72, K766, I85 |
| End-stage renal disease | N18.5,  N18.6, Z49, Z99.2, Z94.0; Procedure codes: 9200; V9200; 9212; V9212; 9314; V9531; DR012; DR013; DR016; DR024; QF006; 9211; V9211; 9213; V9213; V9532; DR015; DR023; DR055; DV056; 9219; V9219; 9223; V9223; DR017; DR020; DR055; DR056; 6070; KAS10; KAS20 |
| Any organ transplantation | Swedish surgery codes (KVÅ codes): KAS, FQA, FQB, GDG, JJC |
| **Comorbidities** | **ICD-10 code** |
| Gastrointestinal diseases | K00-K99 |
| Intestinal infections | A00-A09 |
| Cardiovascular diseases | I00-I99 |
| Obesity/dyslipidemia | E78 , E65, E66 |
| Type 1 and type 2 diabetes | E10-E14 , O24 |
| Autoimmune diseases | E035, E039, E050, E055, E059, E063, E065, G35, M05-M09, M32, L40 |
| Obstructive sleep apnea | G473 |
| Chronic obstructive pulmonary disease (only if diagnosed ≥40 years) | J41-J44 |
| Myositis (no adequate codes present for rhabdomyolysis) | M60 |
| **Medications** | **ATC code** |
| Antibiotics | J01 |
| Proton pump inhibitor | A02BC |
| Antiviral drugs | J05 |
| IBD medications |  |
| Immunomodulators |  |
| Azathioprine | L04AX01 |
| Mercaptopurine | L01BB02 |
| Methotrexate | L04AX03/L01BA01 |
| Anti-TNF treatment |  |
| Infliximab | L04AB02 (L04AA12 before 2008) |
| Adalimumab | L04AB04 (L04AA17 before 2008) |
| Golimumab | L04AB06 |
| Vedolizumab | L04AA33 |
| Systemic corticosteroids |  |
| Betamethasone | H02AB01 |

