| Dexamethasone | H02AB02 |
| Methylprednisolone | H02AB04 |
| Prednisolone | H02AB06 |
| Prednisone | H02AB07 |
| Hydrocortisone | H02AB09 |
| Cortisone | H02AB10 |
| Systemic aminosalicylates (5-ASA) |  |
| Sulfasalazine | A07EC01 |
| Mesalazine | A07EC02 |
| Olsalazine | A07EC03 |
| Balsalazide | A07EC04 |
| Rectal aminosalicylates (5-ASA) |  |
| Mesalazine | A07EC02 |
| Corticosteroids acting locally |  |
| Hydrocortisone | A07EA02 |
| Budesonide | A07EA06 |
| Non-aspirin anti-platelet medications | B01AC excluding aspirin (B01AC06) |
| Aspirin | B01AC06 |
| Non-statin lipid lowering medications | C10AB, C10AC, C10AD, C10AX01-14 |
| Anti-diabetic medications | A10 |
| Anticoagulation medications | B01AA, B01AE, B01AF, B01AX |
| Anti-arrhythmias medications | C01BA, C01BB, C01BC, C01BD, C01BG |
| ATC: Anatomical Therapeutic Chemical; CRC: colorectal cancer; HIV/AIDS: human immunodeficiency virus/ acquired immunodeficiency syndrome; ICD: the International Classification of Disease. | |
| ^a^ ATC codes will be identified from the Prescribed Drug Register; ICD codes and procedure codes will be identified from the National Patient Register. | |
| ^b^ Incident CRC will be ascertained from the Cancer Register, while CRC-related mortality will be ascertained from the Cause of Death Register. In the Cancer Register, all ICD-8, ICD-9, and ICD-10 codes were back-translated to ICD-7. | |
| ^c^ Not at risk of colorectal cancer. | |
| ^d^ Only at risk of rectal cancer. | |
| ^e^ Not at risk of colorectal cancer. | |

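### The propensity score lists IBD treatment as one yes/no item; the SAP should enter and balance-check the Table 2 drug classes separately, because a pooled flag can hide a different treatment mix.

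*SAP*

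**What the plan says.** The covariate list in the SAP, Two-step matching process, has one entry for IBD treatment among ten medication items: "Medications (yes/no, see Table 2 for detail): antibiotics, proton pump inhibitor, antiviral medications, IBD medications". The look-back for these items is "co-medications identified up to and including the index date". No recency window, dose or count is given, so the item is in effect ever/never.

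Table 2 is the code list. Under the IBD medications heading it has sub-headings for:
- immunomodulators (azathioprine, mercaptopurine, methotrexate);
- anti-TNF treatment (infliximab, adalimumab and golimumab, with vedolizumab in the same block);
- systemic corticosteroids (seven codes);
- systemic and rectal 5-ASA;
- locally acting corticosteroids.

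The paragraph that follows the covariate list calls a covariate well balanced when its SMD is below 10%. No section says that the Table 2 classes are separate covariates or separate rows of the balance table. The section on subgroup and sensitivity analyses has none by IBD drug class.

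**The concern.** By listing IBD medications as a covariate, the SAP treats background IBD therapy as a potential confounder. Pooling discards most of what that covariate could carry. A patient with one old mesalazine dispensing scores the same as a patient now on repeated systemic steroids and a biologic. If the classes mark different levels of disease activity, or if any class itself affects the outcomes, matching on the pooled flag does not make the arms alike on that factor. The balance table would not show it, because the SMD is calculated for the pooled item only. Any residual difference would pass into the HRs for CRC, CRC-related mortality and all-cause mortality.

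The SAP does not state how strongly disease activity or 5-ASA use relates to these outcomes, so both are treated below as assumptions.

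**Working it through.** The SAP gives no prevalence of IBD drug use, so it has no figure to reproduce. Its one relevant number is the 10% SMD limit. All prevalences and rate ratios below are assumptions.

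**1. Can a pooled flag pass while the classes differ?**

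For a binary covariate, SMD = (p1 − p0) / √{[p1(1 − p1) + p0(1 − p0)] / 2}, with p1 for statin users and p0 for non-users.

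| Item | p1 v p0 | Absolute SMD | 10% limit |
|---|---|---|---|
| Any IBD drug (pooled) | 90% v 90% | 0.00 | passes |
| 5-ASA | 75% v 60% | 0.15/√0.21375 = 0.32 | fails |
| Steroids or immunomodulators | 20% v 30% | 0.10/√0.185 = 0.23 | fails |
| Biologics | 10% v 15% | 0.05/√0.10875 = 0.15 | fails |

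Patients can use more than one class, so these class figures are compatible with the same 90% total in each arm. A class difference of only about 3, 4 or 5 points (from a base of 10%, 20% or 50%) takes that class past 0.10.

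**2. What could such a difference do to the HR?**

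With no true statin effect, the spurious ratio is [1 + p1(r − 1)] / [1 + p0(r − 1)], where r is the rate ratio linked to the class or to the activity it marks. This approximates the shift in a HR.

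| Assumed factor | p1 v p0 | r | Spurious ratio |
|---|---|---|---|
| Activity marker | 20% v 30% | 1.5 | 1.10/1.15 = 0.957 |
| Activity marker | 20% v 30% | 2.0 | 1.20/1.30 = 0.923 |
| Activity marker | 30% v 45% | 1.5 | 1.15/1.225 = 0.939 |
| Activity marker | 30% v 45% | 2.0 | 1.30/1.45 = 0.897 |
| 5-ASA | 20% v 30% | 0.7 | 0.94/0.91 = 1.033 |
| 5-ASA | 20% v 30% | 0.5 | 0.90/0.85 = 1.059 |

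These scenarios span about 0.90 to 1.06. They are not bounds. Swapping the arms in each gives the reciprocals, about 0.94 (0.85/0.90) to 1.12 (1.45/1.30).

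**3. Does anything else in the score fill the gap?**

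Number of healthcare visits, IBD duration, antibiotics and intestinal infections are in the score and may correlate with activity, but none is specific to it. The gastrointestinal comorbidity item is K00-K99. That range contains K50 and K51, the ICD-10 codes that define IBD in Table 1, so it does not separate mild from severe IBD.

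**4. Is a recent look-back available for everyone?**

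The Prescribed Drug Register "collects information on medications dispensed at all pharmacies in Sweden since July 2005". Statin users are those "with a statin prescription for ≥30 cumulative DDD (cDDD) from July, 2006 or later", and non-users take the index date of their matched user. July 2005 to July 2006 is 12 months, so every index date has at least that much dispensing history.

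**The case against.** The best reply is that the list refers to Table 2 for detail, and that IBD medications is the only medication item there with class sub-headings. Class-level indicators may therefore have been intended. A reader might infer that the score certainly pools the classes; the text does not go that far. Pooling is still the better-supported reading. The control-selection rule uses the term as one set: "random drug prescription (except IBD medications, see Table 2 for ATC codes". Where drugs were meant to be separate, as with aspirin and other anti-platelets, the list names them separately. Mesalazine, A07EC02, sits under both 5-ASA sub-headings, so those two could not be distinct covariates as coded. If class-level entry was intended, the SAP still needs to say so.

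Three other stronger readings are not supported:
- **That nearly every patient is a yes, so the flag passes whatever the mix.** No prevalence is given. Diagnoses go back to 1969 and drug data only to 2005, so some long-standing patients may have no recorded IBD drug. Near saturation the limit is also tight: 95% v 92% gives an SMD of 0.12 and would fail. The flag can pass; it need not.
- **That these drugs are the plan's only handle on disease activity.** The partial proxies above count for something, as do matching on IBD subtype and the exclusion of prior colectomy. They would probably shrink a 10 to 15 point imbalance.
- **That the bias favours statins.** Nothing in the SAP shows which arm has more active disease, and the scenarios move the HR both ways.

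The plan also has E-values, a fracture negative control and removal of early follow-up. These bear on residual confounding in general, but none separates the drug classes. E-values address unmeasured confounding, whereas here measured data would be collapsed.

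**Conclusion.** The point holds in this form: as written, IBD treatment is one ever/never item, class-level entry and class-level balance are not specified, and the 10% check can be met while the treatment mix differs between arms. The SMD arithmetic shows that this is possible, not that it will happen.

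Under assumed imbalances of 10 to 15 points and the rate ratios tabulated, a true HR of 1.00 moves to about 0.90 to 1.06, with the direction unknown. Most single-factor shifts are 3% to 8%. That is modest alone, but it can add to other residual confounding, and it is avoidable with data the plan already defines. It is a cheap improvement that should be made, and no evidence that the results will be wrong.

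**What to change.** In the Two-step matching process section, replace the single item with five yes/no covariates taken from Table 2:
- 5-ASA, as one item because A07EC02 is listed under both the systemic and rectal headings;
- systemic corticosteroids;
- locally acting corticosteroids;
- immunomodulators;
- biologics (the four agents in the anti-TNF block, vedolizumab included).

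Code each as any dispensing in the 12 months before the index date, and report an SMD for each class against the 10% limit. A count of systemic steroid dispensings and a second, ever-use flag are optional.

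Add a sentence noting that the register holds pharmacy-dispensed drugs only. Biologics given elsewhere may be under-recorded, so a good SMD for that class is weaker reassurance than for the others.

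The cost is SAP wording, a few more terms in the logistic model and possibly a few more unmatched statin users. No new data or codes are needed.

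### The propensity score has no antihypertensive item, so hypertension treated only in primary care is not directly captured and may remain unbalanced without the balance check showing it

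*SAP*

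**What the plan says.** The covariates are fixed in the SAP, Two-step matching process, and coded in Table 2. The medication list begins "antibiotics, proton pump inhibitor, antiviral medications, IBD medications, non-aspirin anti-platelet medications" and continues "aspirin, non-statin lipid lowering medications, anti-diabetic medications, anticoagulation medications, and anti-arrhythmias medications". The cardiac drug codes in Table 2 are "C01BA, C01BB, C01BC, C01BD, C01BG", which define the anti-arrhythmic item. No C02, C03, C07, C08 or C09 code appears in the table, and no M01A code.

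On the diagnosis side, Table 2 has one broad item, "Cardiovascular diseases | I00-I99". Its footnote says that "ICD codes and procedure codes will be identified from the National Patient Register". The section on data sources says that this register "covers data on inpatient (since 1964) and outpatient (since 2001) specialist care with disease diagnoses and surgical procedures". No primary-care source is named. The same section says that the Prescribed Drug Register "collects information on medications dispensed at all pharmacies in Sweden since July 2005", with no restriction to specialist prescribers.

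Balance is to be judged by standardized mean differences, with a limit of 10%. No check of variables outside the listed covariates is stated.

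**The concern.** Statins are started largely for cardiovascular risk, and treated hypertension is a plausible accompaniment of that decision. It is also plausibly related to death, and all-cause mortality is a named secondary outcome. A variable related to both belongs in the score if it can be measured.

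The SAP sets drug items beside some diagnoses (anti-diabetic drugs beside diabetes, non-statin lipid drugs beside dyslipidemia), so a condition without a specialist-care code can still be seen. It does not do so for hypertension. A statin user with hypertension managed only in primary care can be paired with a non-user without hypertension, and the two can look identical on every listed covariate. A balance table built from those covariates would then report success. At stake is confounding by indication that could be avoided, chiefly for all-cause mortality and for the number needed to treat derived from it.

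**Working it through.** The SAP gives no prevalence, event count or power figure on this point, so there is no stated figure to reproduce. The check has two parts.

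**1. Can another element of the plan supply the missing information?**

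- *The I00-I99 item* includes hypertension, but only when coded in inpatient or specialist outpatient care. It also merges hypertension with all other circulatory disease.
- *The prescription required of non-users* around the index date can be almost any drug other than an IBD medication, so it does not equalise antihypertensive use.
- *The sensitivity analysis excluding prior CVD* states no definition other than I00-I99 from the same register. It would keep the patients whose hypertension has no specialist-care code.
- *The time-varying model* names no further covariates.
- *E-values and the fracture negative control* address unmeasured confounding in general. Neither measures this imbalance.
- *Availability of the data:* the drug register starts in July 2005 and qualifying statin use in July 2006, so at least 12 months of dispensing history precede every index date.

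**2. How large could the effect be?**

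All inputs here are assumptions. Let p1 and p0 be the proportions on antihypertensives among users and non-users after matching. Let RR be the mortality ratio for antihypertensive use given the other covariates.

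- Bias factor = (1 + p1(RR − 1)) / (1 + p0(RR − 1))
- SMD = (p1 − p0) / √[(p1(1 − p1) + p0(1 − p0)) / 2]

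| p1 vs p0 | SMD | RR 1.1 | RR 1.2 | RR 1.5 |
| --- | --- | --- | --- | --- |
| 50% vs 45% | 0.10 | 1.005 | 1.009 | 1.020 |
| 55% vs 45% | 0.20 | 1.010 | 1.018 | 1.041 |
| 60% vs 40% | 0.41 | 1.019 | 1.037 | 1.083 |
| 65% vs 35% | 0.63 | 1.029 | 1.056 | 1.128 |

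The two extremes worked through:

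- Smallest: (1 + 0.50 × 0.1) / (1 + 0.45 × 0.1) = 1.050 / 1.045 = 1.005
- Largest: (1 + 0.65 × 0.5) / (1 + 0.35 × 0.5) = 1.325 / 1.175 = 1.128

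A middle case, 60% vs 40% with RR 1.3, gives 1.18 / 1.12 = 1.054. The first row sits at the SAP's own 10% limit, and the bias there is at most about 2%.

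The factor exceeds 1 because users are assumed to be treated more often and treatment is assumed to mark higher risk. The mortality hazard ratio would then be too high, which works against the hypothesised benefit. The formula is exact for a risk or rate ratio and is used here as an approximation for the hazard ratio.

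**The case against.** A reader might infer that cardiovascular risk treated in primary care stays unbalanced. The documents do not support that, for two reasons.

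First, it is too broad. Six drug items already pick up part of this risk wherever the drug was prescribed: aspirin, other antiplatelets, anticoagulants, anti-arrhythmics, anti-diabetics and non-statin lipid drugs. The gap is treated hypertension without a specialist-care code. It may be narrower still, because every cohort member has an IBD code in the National Patient Register and hypertension could be recorded at such contacts. The SAP does not say how often it is.

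Second, an actual imbalance is not shown. Age at IBD diagnosis and IBD duration together give age at index, and diabetes, obesity/dyslipidemia, aspirin and number of healthcare visits are also in the score. These are plausibly correlated with antihypertensive use and may balance it in part. The post-matching gaps used above are inputs, so an SMD above 10% in the table is not a result.

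Three further points are fair. The bias, in the direction assumed, is conservative for mortality. No effect on the primary outcome, incident CRC, has been quantified. And any covariate list can be extended, so a longer one is not automatically better.

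A reader might also fold non-aspirin NSAIDs or nitrates into the same argument. They do not share it. NSAIDs would matter, if at all, for CRC, and possibly in the other direction: with an assumed RR of 0.7 to 0.8 and use commoner in users (50% vs 45% to 60% vs 30%), the factor is 0.90 to 0.99. The SAP supports neither that effect nor that difference in use.

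What remains is that the omission is certain, the data are already held, and none of the planned safeguards measures this imbalance.

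**Conclusion.** The point holds in a limited form. The score has no antihypertensive item and diagnoses come only from specialist care, so hypertension treated only in primary care is not directly captured. It may remain unbalanced, and the planned balance check would not reveal it.

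The size is unknown from the documents. Under the stated assumptions the all-cause mortality hazard ratio would be multiplied by about 1.005 to 1.13, with 1.05 in the middle case. That could mask part of a benefit and distort the number needed to treat; in this direction it would not create a spurious mortality benefit. If non-users were the more often treated, the direction would reverse.

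This is an inexpensive improvement that should be made. It does not show that the matched comparison is invalid.

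**What to change.** Add one yes/no item for antihypertensive drugs (ATC C02, C03, C07, C08, C09), taken from the Prescribed Drug Register up to and including the index date, to Table 2, the propensity score and the balance table.

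The modification history and the list of non-prespecified analyses show that the third version followed external reviewers' comments, so the matched cohort may already be fixed. In that case leave the main analysis as it stands, report the post-matching SMD for antihypertensive use, and run a sensitivity analysis, labelled as added, that either re-matches with the item or adjusts for it.

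As a separate, secondary point about CRC, dispensed non-aspirin NSAIDs (M01A) can be added in the same way. The report should note that the register is described as covering dispensed medications, so non-prescription use may not be captured.

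The cost is a few ATC codes from a register already held and one further run. Slightly fewer statin users may find a match within the caliper.
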